**Secondary Endpoints:**

1. Incidence and severity of COVID-19 (mild/moderate/severe).
2. Overall survival (OS) at one year.
3. Time to first SARS-CoV-2 infection.
4. Incidence of adverse events related to plasma infusion.
5. SARS-CoV-2 antibody titers and their kinetics over time.

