3.2 Secondary Objectives

1. To assess the severity and clinical course of COVID-19 infection (mild, moderate, severe, or critical) in CCP versus control groups.

2. To evaluate overall survival (OS) at one year post-transplant.

3. To determine the time to first SARS-CoV-2 infection after transplantation.

4. To assess the kinetics and durability of anti–SARS-CoV-2 antibody levels following CCP infusion.

5. To evaluate the safety and tolerability of CCP administration by recording infusion-related and systemic adverse events.

6. To explore correlations between antibody titers and clinical outcomes.

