3.4 Secondary Endpoints

1. COVID-19 severity grading according to WHO Clinical Progression Scale (scores 1–10).

2. Overall survival rate at 12 months post-transplant.

3. Time to first COVID-19 diagnosis (days from transplantation to first positive test).

4. Quantitative or semiquantitative SARS-CoV-2 antibody titers measured at predefined intervals (baseline, pre-infusion, and 14, 28, 60, 90, 180, and 365 days post-transplant).

5. Number and proportion of adverse events (AEs) and serious adverse events (SAEs) related to plasma infusion, graded according to CTCAE v5.0.

6. Association between CCP antibody titer and risk reduction for COVID-19 infection or severe disease.

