**Ⅴ. Statistical Considerations**

5.1 Sample Size Determination

The sample size was calculated based on the expected difference in the incidence of COVID-19 infection between the CCP group and the control group.

According to preliminary clinical observations and published data, the infection rate within one year after HSCT was estimated at 80% in the control group and 50% in the CCP group.

Assuming a two-sided significance level (α = 0.05) and a statistical power of (1 – β = 0.80), and using a log-rank test for comparison between groups, the required total sample size was calculated to be 72 participants (36 per group).

This number also accounts for an estimated 10% attrition rate due to loss to follow-up or early withdrawal.

The sample-size calculation was performed using PASS software version 15.0 (NCSS, Kaysville, UT, USA).

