5.3 Statistical Methods

1. Descriptive Statistics:

Continuous variables will be summarized as mean ± standard deviation (SD) or median (interquartile range, IQR) as appropriate.

Categorical variables will be summarized as counts and percentages.

2. Group Comparisons:

Continuous variables: Student’st-test (normally distributed) or Mann–WhitneyU test (non-normally distributed).

Categorical variables: Chi-square (χ²) or Fisher’s exact test.

Time-to-event data (e.g., infection-free survival): Kaplan–Meier analysis and log-rank test.

3. Multivariate Analysis:

Cox proportional-hazards regression will be used to identify independent factors associated with infection risk or survival.

Variables withP < 0.10 in univariate analysis will be included in the multivariate model.

4. Confidence Intervals:

Two-sided P values < 0.05 will be considered statistically significant.

For all main comparisons, 95% confidence intervals (CIs) will be reported alongside P values.

5. Correction for Multiple Comparisons:

When multiple secondary endpoints are analyzed,P values will be adjusted using the Benjamini–Hochberg false discovery rate (FDR) method to control for type I error.

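### The Benjamini–Hochberg rule for secondary endpoints has no exemption for safety, so it can only make a harm look less significant in the final report

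*Protocol*

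**What the plan says.** Protocol section 5.3, item 5 sets the multiplicity rule: "When multiple secondary endpoints are analyzed,P values will be adjusted using the Benjamini–Hochberg false discovery rate (FDR) method to control for type I error". It names no endpoint that is left out.

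Safety is one of the secondary endpoints. Section 3.4, item 5 reads "Number and proportion of adverse events (AEs) and serious adverse events (SAEs) related to plasma infusion, graded according to CTCAE v5.0", and the Study Summary lists "Incidence of adverse events related to plasma infusion" as item 4 of 5. The matching objective in section 3.2 is wider: "To evaluate the safety and tolerability of CCP administration by recording infusion-related and systemic adverse events". Survival is also in the list: "Overall survival rate at 12 months post-transplant" (section 3.4, item 2).

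The significance criterion is in section 5.3, item 4: "Two-sided P values < 0.05 will be considered statistically significant". The same item adds "For all main comparisons, 95% confidence intervals (CIs) will be reported alongside P values", without saying which comparisons count as main. Section 5.2 places control patients in the safety population, so a between-arm safety comparison is possible.

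Sections 4.6, 5.5 and 6.3 govern safety during the trial: grading, expedited SAE reporting, and DSMB review with discretion to act on a signal. None of them refers to a P value.

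**The concern.** A false discovery rate procedure limits the share of claimed effects that are false. That is what is wanted when several secondary endpoints could each support a claim for plasma. For harm, the costly error is the missed signal. A Benjamini–Hochberg (BH) adjusted P value is never smaller than the raw one, so including safety moves every harm result towards non-significance. How far it moves depends on results that have nothing to do with harm, such as antibody titre or time to infection.

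The final safety statement is at stake. Section 2.4 says that the trial will give evidence on safety and describes the approach as low in toxicity. An AE excess with a raw P below 0.05 could be reported as not significant only because of the family it sits in.

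**Working it through.** **Inputs from the protocol.** 36 patients per arm and two-sided α = 0.05 (section 5.1); chi-square or Fisher's exact test for proportions (section 5.3, item 2); a family of m = 5 (Study Summary list) or m = 6 (section 3.4 list). The protocol gives no AE rates and no power for harm, so there is no figure of its own to reproduce. The AE and survival rates below are assumptions.

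**BH thresholds.** The endpoint ranked k-th smallest of m is compared with 0.05 × k/m. Antibody titre is very likely to give a tiny P value, since one arm receives high-titre plasma and the other none. The harm endpoint then ranks second at best:
- m = 5: 0.05 × 2/5 = 0.020
- m = 6: 0.05 × 2/6 = 0.0167

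If two other endpoints have smaller P values, the thresholds are 0.05 × 3/5 = 0.030 and 0.05 × 3/6 = 0.025.

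**Case 1: plasma-related AEs, Fisher's test.** Controls receive no plasma, so their rate is taken as 0%. With 0/36 in controls, the two-sided P for x/36 in the plasma arm is 2 × C(36,x)/C(72,x).
- x = 6: 2 × 1,947,792/156,238,908 = 0.0249
- x = 7: 0.0113

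Unadjusted, 6 events are enough. With titre significant, 0.0249 exceeds both 0.020 and 0.0167, so 7 are needed. With two other endpoints significant, 0.0249 is below both 0.030 and 0.025, so 6 are enough again.

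For a true plasma-arm rate of 20%, X ~ Binomial(36, 0.20):
- unadjusted: P(X ≥ 6) = 0.754
- titre significant, fixed threshold: P(X ≥ 7) = 0.599; simulating the full BH procedure with the other P values uniform gives 0.61
- two others significant: 0.754, no loss

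A result of 6/36 versus 0/36 has raw P = 0.025. With titre significant and no larger P value pulling it down, the adjusted P is 0.0249 × 5/2 = 0.062 or 0.0249 × 6/2 = 0.075.

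**Case 2: any AEs compared between arms, chi-square test, 10% versus 30%.** Summing the two binomials over all tables that reject in the harm direction:
- unadjusted at 0.05: 0.579
- titre significant, fixed thresholds: 0.423 (m = 5) and 0.388 (m = 6); simulating full BH gives 0.429 and 0.396

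Power therefore falls from about 58% to 39–43%. As an example, 12/36 versus 4/36 gives χ² = 72 × (12×32 − 24×4)²/(36×36×16×56) = 5.14, P = 0.023. With titre significant and m = 5 the adjusted P is 0.0233 × 5/2 = 0.058.

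**Survival read as harm (assumed 80% versus 60% alive at one year).** Expected deaths are 36 × (0.20 + 0.40) = 21.6. The hazard ratio is ln 0.6/ln 0.8 = 2.29. The Schoenfeld statistic is √21.6/2 × ln 2.29 = 1.92. Power is Φ(1.92 − 1.96) ≈ 49% at 0.05 and Φ(1.92 − 2.39) ≈ 32% at 0.0167.

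**What zero events would show.** With 0/36 related SAEs, the two-sided 95% upper limit is 1 − 0.025^(1/36) = 9.7%.

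**The case against.** Several counter-arguments carry weight.

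- **No safety action depends on a P value.** SAE reporting and DSMB review run on clinical judgement (sections 4.6, 5.5, 6.3). This stands. A reader might infer that patient protection during the trial is weakened; the documents do not support that.
- **The loss is not certain.** A reader might infer that real harm will be adjusted into non-significance. The BH threshold runs from 0.05/m up to 0.05, and large harms often survive it. The worst case needs no other endpoint to differ, which is implausible with antibody titre in the family.
- **The trial does not miss most relevant harms.** A reader might infer that it does. In the two AE cases worked here, unadjusted power is 75% and 58%. Smaller excesses fare worse: 5% versus 15% has about 15% power with Fisher's test. That comes from 36 per arm, not from BH.
- **The listed endpoint is plasma-related events, which controls cannot have.** This stands, and Case 1 uses a 0% control rate for that reason. It also makes a between-arm P value for that endpoint of limited meaning, which is a further reason not to let an adjusted one decide. Case 2 applies only if systemic AEs, named in the section 3.2 objective, are compared between arms.
- **Confidence intervals are already promised, and BH does not change them.** This is partly right, but the promise covers undefined main comparisons and safety is not named.
- **Adjusting survival is ordinary.** This is true for a claim of benefit. Exempting survival only when it goes against plasma would let the observed direction decide the analysis, so that is no remedy.
- **The make-up of the family could be left to the SAP.** A SAP may narrow it, but the protocol already states a rule, and as stated that rule includes safety.

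**Conclusion.** The point holds as a defect in the rule for final reporting. Section 5.3, item 5 puts safety into the BH family, where adjustment works in the wrong direction. With antibody titre significant, the cost is about 14 percentage points of power for plasma-related AEs at 0% versus 20% (75% to 61%) and none if two other endpoints are also significant. It is about 15 to 19 points for any AEs at 10% versus 30% (58% to 39–43%).

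These figures rest on assumed event rates, a family of 5 or 6, independent endpoints, and all 36 patients per arm being evaluable. The limited power for harm is due mainly to the sample size, and BH adds to it. The protocol does not say that a safety conclusion will be drawn from a non-significant result, but nothing in it rules that out.

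**What to change.** In section 5.3, item 5:

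1. Limit the BH adjustment to the secondary efficacy and antibody endpoints.
2. State that AE and SAE comparisons are reported unadjusted, as proportions and risk differences with 95% confidence intervals, and that no safety conclusion is drawn from P > 0.05. The 9.7% upper limit after zero related SAEs in 36 patients shows why.
3. Keep any claim of survival benefit in the BH family, but always report the survival hazard ratio or difference with an unadjusted 95% confidence interval, whatever its direction.

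This takes a few sentences and no extra patients, visits or data. The price is a somewhat higher chance of a false safety signal. The change does not raise the power that 36 per arm gives for harm.

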5.4 Missing Data

No imputation will be performed for missing primary endpoint data.

Participants who withdraw before infection assessment will be censored at the date of last follow-up.

Sensitivity analyses will compare results between complete-case and ITT datasets to ensure robustness.

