3.3 Primary Endpoint

Incidence of laboratory-confirmed SARS-CoV-2 infection within 12 months after HSCT.

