5.2 Analysis Populations

Three analysis populations will be defined:

1. Intention-to-Treat (ITT) population:

Includes all randomized participants, analyzed according to the group to which they were originally assigned, regardless of treatment received.

2. Per-Protocol (PP) population:

Includes participants who complete all planned study procedures and at least four CCP infusions (for the CCP arm) without major protocol violations.

3. Safety population:

Includes all participants who receive at least one CCP infusion (in the experimental group) or standard care (in the control group), used for safety analyses.

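### The protocol's stated missing-data check compares two analyses that both assume non-informative dropout, so agreement between them does not establish robustness

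*Protocol*

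**What the plan says.** The primary endpoint (section 3.3) is "Incidence of laboratory-confirmed SARS-CoV-2 infection within 12 months after HSCT". Section 5.2 defines the ITT population as follows: "Includes all randomized participants, analyzed according to the group to which they were originally assigned, regardless of treatment received".

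Section 5.4 then makes three statements:

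- It bars filling in unknown outcomes: "No imputation will be performed for missing primary endpoint data".
- It handles people who leave early by censoring, in these terms: "Participants who withdraw before infection assessment will be censored at the date of last follow-up".
- It closes by naming the check at issue here: "Sensitivity analyses will compare results between complete-case and ITT datasets to ensure robustness".

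Section 5.3 offers two routes for comparing infection between arms. One is "Time-to-event data (e.g., infection-free survival): Kaplan–Meier analysis and log-rank test", which fits the censoring rule and the log-rank basis of the sample size in section 5.1. The other is "Categorical variables: Chi-square (χ²) or Fisher’s exact test", which would apply if one-year incidence were compared as a simple proportion.

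The protocol does not define complete-case. It describes no other analysis that varies what is assumed about participants who leave. The per-protocol analysis addresses adherence, not missing outcomes.

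**The concern.** A missing-data sensitivity analysis is informative when it changes the assumption that cannot be checked from the data. Here that assumption is that participants who leave have the same later infection risk as comparable participants who stay. The censored ITT analysis makes that assumption, and so does a complete-case analysis. Setting one against the other changes how much partial follow-up is used, but not the assumption itself.

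The matter is practical in this trial. Section 4.3 leaves investigators and participants unblinded, so reasons for leaving may differ by arm. Section 5.1 expects 10% attrition. The section 4.7 table lists PCR tests only up to 3 months, and the Figure 1 caption ends testing at day +120, while the endpoint runs to 12 months. Late infections are therefore found mainly among people who remain in contact. If the two analyses agree, section 5.4 invites the report to call the result robust when the question has not been tested.

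**Working it through.** **Inputs from the protocol.** There are 36 participants per arm, two-sided α is 0.05 and attrition is 10% (section 5.1). On event rates, section 5.1 states that "the infection rate within one year after HSCT was estimated at 80% in the control group and 50% in the CCP group". The plan attaches no figure to its sensitivity analysis, so there is none to reproduce. The number of missing outcomes and their split by infection status are assumptions throughout.

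**Step 1: binary comparison.** With no imputation, a participant whose 12-month status is unknown enters neither numerator nor denominator. The unimputed ITT proportion and the complete-case proportion then use the same people. For example, 26/32 vs 16/32 gives chi-square p = 0.0085 in both sets.

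**Step 2: censored log-rank.** Here the sets differ, because ITT keeps the partial follow-up of withdrawals. A simulation shows how often the verdicts differ. It used 36 per arm, exponential infection times, 12 months of follow-up and 1,500 replicates, and took complete-case to mean that withdrawals are excluded.

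| Scenario (assumed) | Missing | Estimated difference, ITT / complete-case | Rejection, ITT / complete-case | Same verdict |
|---|---|---|---|---|
| No true effect (80% both arms); 25% of CCP infections lost just before detection | about 10% | 0.100 / 0.054 | 18.5% / 7.9% | 88% |
| No true effect; half of uninfected controls leave early | 5% | 0.082 / 0.086 | 11.7% / 14.2% | 97% |
| True difference 0.30; 20% of CCP infections lost | about 5% | 0.373 / 0.355 | – | 96% |
| No true effect; 40% of CCP infections lost | 16% | 0.181 / 0.097 | 40% / 12% | 71% |

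When 10% withdraw for reasons unrelated to infection, the verdicts agree in 96–99% of trials. Agreement therefore looks much the same with or without informative dropout, except when the loss is heavy and one-sided.

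**Step 3: how far missing outcomes could move the result.**

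*(a) Every leaver has an unknown outcome.* 10% × 36 = 3.6, so 3 or 4 per arm. The extreme bound counts missing CCP participants as infected and missing controls as uninfected (uncorrected chi-square).

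- 4 missing per arm: 26/32 vs 16/32, p = 0.0085, becomes 26/36 vs (16 + 4)/36 = 20/36, p = 0.141.
- 3 missing per arm: 26/33 vs 16/33, p = 0.0105, becomes 26/36 vs (16 + 3)/36 = 19/36, p = 0.088.
- Opposite bound with 4 missing: (26 + 4)/36 = 30/36 vs 16/36, p = 0.0006.

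*(b) Leavers who were already infected have a known outcome.* Take a loss hazard μ = −ln(0.9) = 0.105 per year and an infection hazard λ = −ln(1 − risk), which is 1.609 for control and 0.693 for CCP. The observed infected fraction is λ/(λ+μ) × [1 − exp(−(λ+μ))]. The fraction followed uninfected to 12 months is (1 − risk) × 0.9.

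- Control: 0.770 + 0.180 = 0.950 known, so 36 × 0.050 = 1.8 missing.
- CCP: 0.477 + 0.450 = 0.927 known, so 36 × 0.073 = 2.6 missing.

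Rounded, the observed data are 28/34 vs 17/33 (chi-square p = 0.007, Fisher p = 0.010). The worst case is 28/36 vs (17 + 3)/36 = 20/36, with chi-square p = 0.0455 and Fisher p = 0.079.

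**The case against.** **The check is not empty.** A reader might infer that it can never reveal informative dropout and reports robustness automatically. The documents do not support that. It is true only for an unimputed proportion, whereas sections 5.1, 5.3 and 5.4 point to a censored log-rank test. Under that test the sets differ, and with heavy one-sided loss the verdicts differed in 29% of simulated trials (100% − 71%). The check can sometimes give a warning. This stands.

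**The bounds are extreme.** The 4-per-arm case needs all missing CCP participants infected and all missing controls uninfected. Under the planned rates and non-informative loss, that has probability 0.5⁴ × 0.2⁴ = 0.0001. The p-values also come from chi-square tests, not the log-rank. Calculation (b) shows that 10% loss may leave only 2 to 3 outcomes unknown per arm, where the worst case falls on either side of 0.05 depending on the test. This stands too: the figures are limits, not forecasts.

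**A statistical analysis plan may add more.** One may exist, and tipping-point methods are often placed there, so their absence from the protocol is not a fault in itself. That does not remove the point. The protocol names a specific check and says what it is for, and that check cannot deliver it.

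**Conclusion.** The concern holds in a limited form. The comparison in section 5.4 sets two analyses side by side that share the assumption of non-informative dropout. They are identical for an unimputed proportion, and they usually, but not always, agree under the censored log-rank even when both are biased. Agreement therefore does not establish robustness.

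The possible effect on the conclusion ranges from borderline (chi-square p = 0.046, Fisher p = 0.079, with 2 to 3 missing per arm) to clear loss of significance (p = 0.14, with 4 missing per arm). Both are worst-case bounds at roughly the planned rates. They rest on an assumed split of missing outcomes, and the simulated dropout patterns are likewise assumptions; the protocol gives only the 10%.

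Nothing here shows that dropout will be informative or that the main analysis is wrong. The protocol should be changed on this point, but the primary analysis can stand.

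**What to change.** Keep the censored ITT log-rank as the main analysis. Replace the last sentence of section 5.4 with an analysis in the ITT set that varies the missing-data assumption:

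- A delta-adjusted tipping-point analysis: impute infection after withdrawal and raise the post-withdrawal hazard in the CCP arm step by step (for example ×1, 1.5, 2, 3 and upward) until p exceeds 0.05. Report the multiplier at which this happens, so that readers can judge whether it is plausible. The grid is one reasonable choice among several.
- Best- and worst-case results, labelled as bounds.
- The number, timing and reasons for withdrawal by arm.

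If the complete-case comparison is kept, define the set and describe it as descriptive.

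The cost is a changed sentence and a little more programming in R, which section 5.6 already names. No new data are needed. The downside is that the result may look less robust.

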5.5 Interim and Safety Analysis

An interim safety review will be conducted after the first 20 participants complete all four CCP infusions.

The Data and Safety Monitoring Board (DSMB) will review adverse events, infection incidence, and survival data.

If any safety signal or unexpected event (e.g., transfusion-related acute lung injury) is detected, the DSMB may recommend protocol modification or early termination.

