**Sample Size:**

72 participants (36 per group), calculated assuming infection rates of 80% in the control group and 50% in the CCP group, α = 0.05, β = 0.20, using a log-rank test.

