**Figure 1. Study schedule.**

**Timeline of convalescent plasma (CCP) infusions and virological/immunological monitoring after HSCT. CCP infusions were given on days +14, +28, +60, and +90. Twice-weekly nucleic acid and weekly antibody testing continued through day +120.**

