4.2 Randomization and Allocation Concealment

Randomization is performed using a computer-generated sequence prepared by an independent statistician who is not involved in patient care.

Allocation follows a simple randomization design with a 1:1 ratio between the CCP group and the control group. The randomization sequence is stored securely by the data manager and concealed until the time of patient enrollment.

Upon confirmation of eligibility and signed informed consent, the investigator obtains the next available randomization code from the sealed allocation list. This process ensures that treatment assignment remains concealed until enrollment is finalized.

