4.4 Intervention

4.4.1 Experimental Group (CCP Group)

Participants receive standard supportive care plus four infusions of high-titer COVID-19 convalescent plasma (CCP).

Dosage: 200 mL per infusion.

Infusion schedule:

1. Day +14 ± 2 days
2. Day +28 ± 2 days
3. ~2 months (±7 days)
4. ~3 months (±7 days)

Each CCP unit must meet the following criteria:

Collected from donors who have fully recovered from COVID-19 and are at least 14 days symptom-free.

Confirmed SARS-CoV-2 PCR negative at the time of donation.

Tested positive for anti–SARS-CoV-2 IgG with high antibody titer (S/CO ≥ 12) according to ELISA testing standards.

ABO compatible with the recipient.

Infusions are administered intravenously at a rate not exceeding 2 mL/kg/hour, with continuous monitoring for transfusion reactions.

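### The only scheduled interim safety review is triggered by 20 four-infusion completers, so it comes late, moves later as completion falls, and may never occur

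*Protocol*

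**What the plan says.** Section 5.5 schedules one interim review: "An interim safety review will be conducted after the first 20 participants complete all four CCP infusions". At that review the DSMB looks at adverse events, infection incidence and survival. The section adds that the DSMB may recommend modification or early termination if a safety signal or unexpected event is found.

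Section 5.1 and the study summary plan 72 participants, 36 per group. Section 4.2 states: "Allocation follows a simple randomization design with a 1:1 ratio between the CCP group and the control group". The legend of Figure 1 gives the schedule: "CCP infusions were given on days +14, +28, +60, and +90". Section 4.4.1 allows ±7 days around the fourth infusion.

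Other safety provisions bear on the point:
- Section 4.6 sends all SAEs to the principal investigator within 24 hours, with ethics committee review, and gives the DSMB general oversight.
- Section 6.3 sends SAEs suspected to be related to CCP to the ethics committee and the DSMB within 24 hours. It also discontinues the infusion for a Grade 3 or higher event.
- Section 5.2 defines a safety population of everyone with at least one CCP infusion, plus controls on standard care.

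The protocol states no accrual rate, no enrolment pause and no earlier scheduled review.

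**The concern.** The trigger counts completion of treatment, not exposure to it. Two consequences follow.

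First, the review waits until 20 members of a 36-patient arm have each been through about two and a half months of infusions, while enrolment continues behind them.

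Second, a participant who dies, withdraws or stops infusions never counts, so poorer tolerability delays the review. Under section 6.3 a participant whose infusion is discontinued may also fail to count.

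What is at stake is the one planned occasion on which the DSMB compares the arms. An excess of deaths or infections, each judged unrelated to plasma in an open-label trial, shows up only in such a comparison.

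**Working it through.** **Inputs from the protocol.** Trigger: 20 completers (5.5). CCP arm: 36 planned (5.1). Infusions on days +14, +28, +60 and +90 (Figure 1), so 90 − 14 = 76 days from first to fourth, or 76/30.4 = 2.5 months.

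**Assumptions.** Total accrual of 4 to 12 patients per month, so 2 to 6 per month in the CCP arm and 72/4 = 18 down to 72/12 = 6 months of enrolment. Entry near day +14. Completion share c varied. The only related figure in the protocol is in 5.1: "This number also accounts for an estimated 10% attrition rate due to loss to follow-up or early withdrawal".

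**The plan's own figure.** The denominator is 36 per arm. From "the infection rate within one year after HSCT was estimated at 80% in the control group and 50% in the CCP group" the implied hazard ratio is ln 0.5 / ln 0.2 = 0.431. The Schoenfeld formula (two-sided 0.05, 80% power) needs 45 events, and 45/0.65 = 69.2, so N = 70 without attrition and 70/0.9, rounded up, = 78 with 10%. The stated 72 is thus close to the figure without attrition. That is a separate matter: an arm of 39 would change the minimum share below only from 20/36 to 20/39 = 51%. I use 36 as planned.

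**Minimum share randomised at the review.** 20/36 = 55.6%, with no accrual assumption. By then at least 20 × 4 = 80 of 36 × 4 = 144 planned infusions have been given.

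**Expected number of CCP participants randomised at the review.** min(36, 20/c + CCP accrual per month × 2.5):

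| Completion c | 4 per month | 8 per month | 12 per month |
|---|---|---|---|
| 100% | 20 + 5 = 25 | 20 + 10 = 30 | 20 + 15 = 35 |
| 90% | 22.2 + 5 = 27.2 | 22.2 + 10 = 32.2 | 36 (cap) |
| 80% | 25 + 5 = 30 | 25 + 10 = 35 | 36 (cap) |
| 70% | 28.6 + 5 = 33.6 | 36 (cap) | 36 (cap) |

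Slower accrual does not remove the effect: over 36 months with full completion the figure is 22.5 of 36 (62%). A simulation with simple randomisation agrees. At 90% completion and 12 months' accrual, the median is 29 CCP participants and 59 of 72 overall.

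**Delay caused by non-completion.** (20/c − 20) / CCP accrual. At c = 90%: 2.2/6 = 0.4 to 2.2/2 = 1.1 months. At c = 80%: 5/6 = 0.8 to 5/2 = 2.5 months.

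**Chance that the trigger is ever reached.** P(X ≥ 20), X binomial(36, c): above 99.9% at c = 0.9, 97.8% at 0.7, 76% at 0.6, 31% at 0.5. Simple randomisation does not guarantee 36 in the arm. Allowing for that, the simulation never reached the trigger in about 1% of trials at c = 0.8 and 7 to 8% at c = 0.7.

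**What remains at the review with full completion.** The 5 to 15 participants in mid-course have had on average (14×1 + 32×2 + 30×3)/76 = 2.2 infusions. Infusions given are 80 + 5×2.2 = 91 to 80 + 15×2.2 = 113 of 144, so about 21 to 37% are still to come.

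**Routes to the DSMB outside the review.** Section 6.3 covers related SAEs only. Section 4.6 covers all SAEs, but its 24-hour route ends with the principal investigator, followed by ethics committee review. Its oversight sentence fixes no meeting or data cut.

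**The case against.** A reader might infer that the review looks only at participants who tolerated treatment. The protocol does not support that. Only the trigger counts completers; 5.5 places no such limit on the data, and the safety population in 5.2 includes everyone with one infusion, plus controls.

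A reader might also infer that nothing protects participants before the review, or that little is left to protect once it happens. Neither follows. Related SAEs reach the DSMB within 24 hours, the DSMB has continuing oversight, and its power to recommend changes is not expressly tied to the scheduled review. The risks named in 6.3 are transfusion reactions, which individual reporting is well suited to catch. Some 21 to 37% of infusions are still to come at the review under the assumptions above, as is follow-up to 12 months.

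Nor is it right that any harm delays the review: only harm that prevents completion does. At the protocol's 10% attrition the delay is about a month or less. The DSMB charter is not shown and may set further meetings.

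The present trigger also has a merit: it ensures a look at cumulative exposure. A day +28 look in its place would leave infusions three and four without a scheduled review.

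All of this stands and limits the consequence. It does not answer the narrower point: the rule as written moves the one scheduled comparative review the wrong way when completion falls, and SAEs judged unrelated have no stated 24-hour route to the DSMB.

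**Conclusion.** The concern holds as a weakness in how the trigger is defined, not as an absence of safety monitoring. Without any assumption on accrual, at least 56% of the planned CCP arm is randomised by the review. At an assumed 4 to 12 patients per month it is 25 to 35 of 36 with full completion and 30 to 36 at 80% completion. Near or below 20/36 completion the review may never be triggered.

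The exact timing depends on the assumed accrual and completion and on entry near day +14. The study summary admits patients up to day 100; late entrants could not receive all four infusions on the stated schedule, which would slow the count further. The entry window and the schedule need to be reconciled.

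The wording also leaves open whether the count means the first 20 to complete, as taken here, or the first 20 treated all completing. On the second reading one early death leaves the trigger unmet.

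The change is worth making, because following the stated rule delays the review when tolerability is worse.

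**What to change.** In 5.5, trigger the review on exposure: it takes place when the first 20 participants who received at least one CCP infusion have either reached the time of their planned fourth infusion, or stopped or died earlier. State that it covers the whole safety population to date, with concurrent controls shown beside the treated participants.

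This makes the timing independent of completion and guarantees that the review occurs once 20 have been treated. It does not bring the review forward when everyone completes: 25 to 35 of 36 would still be randomised at the assumed accrual.

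If an earlier view is wanted, add one safety-only look, for example when the first 10 treated participants reach day +28. That falls at about 10 + 2×14/30.4 = 11 to 10 + 6×14/30.4 = 13 CCP participants randomised. It should be in addition to the later review, not in place of it. Keeping it to safety data avoids a further comparative look at infection, the primary endpoint.

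The cost is a short change to 5.5, a matching line in the DSMB charter and possibly one more meeting. The early look carries limited information: with 10 participants, the chance of seeing at least one event of 5% frequency is 1 − 0.95^10 = 40%, against 64% with 20.
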